## Abstract

Background: Despite substantial improvements in antenatal care and skilled birth attendance coverage, postpartum service uptake lags in the Lao People's Democratic Republic (Lao PDR). The 2019 Lao Primary Health Care Policy emphasizes the importance of village health volunteers/workers (VHVs/VHWs) working as groups or pairs to promote primary care services, including obstetric care. However, little is known about whether or how the pairing of male and female VHVs/VHWs may encourage better uptake of postpartum care in communities with solid gender norms.

Objective: Therefore, the study aims to assess the effectiveness of male-female VHVs/VHWs working in pairs on women's uptake of facility-based follow-up PNC visits in rural Sepone, Lao PDR.

Methods: A quasi-experimental cluster study will be conducted between July 2024 and October 2026 in 37 selected sites from two districts in the southern Lao PDR. In 19 selected intervention villages in the Sepone district, trained female-male VHVs/VHWs pairs will promote postpartum services, whereas in 18 similar control villages in the Vilabuly district, VHVs/VHWs will implement standard activities for obstetric care promotion. The study obtained ethical approvals from the University of the Ryukyus and the Lao Tropical and Public Health Institute.

Data analysis: Difference-in-difference analyses will be conducted to estimate service coverage pre-post intervention changes in study sites. Then, using mixed-effect binary logistic regressions, we will assess the association between pairing VHVW/s and facility-based follow-up PNC use, which will be adjusted for other covariates and time effects. Finally, we will analyze the context of pairing VHVs/VHWs implementation using coded transcripts of interviews and focus group discussions.

Results: At the end of the study period, we anticipate at least a 10% increase in follow-up PNC visits at intervention sites compared to control sites. The improvement is expected to result from improved mothers' trust and satisfaction with VHVs/VHWs, and enhanced husband support.

Conclusion: The findings of this study will guide the Lao government's strategy to involve both male and female VHVs/VHWs in primary healthcare according to the 2019 Primary Health Care Policy.

## Introduction

Access to equitable, timely, and people-centered quality maternal and child health (MCH) services continues to be a significant global challenge, especially in developing countries [1]. In 2020, approximately 287,000 mothers and five million children under five died worldwide from preventable causes, primarily in sub-Saharan Africa and southern Asia [2,3].

The Lao People's Democratic Republic (Lao PDR) has made substantial progress in recent decades in improving basic obstetric care coverage and reducing maternal and neonatal deaths [4,5]. According to Lao Social Indicator Surveys, the proportion of pregnant women who utilized antenatal care (ANC) provided by a skilled health professional four times increased from 54.2% in 2012 to 89.8% in 2023, and skilled birth attendance coverage rose from 41.5% in 2012 to 79.8% during the same period [6,7]. However, postnatal care (PNC) continues to lag behind other services, with an increase of only 39.5% to 64.2% in the same period. Moreover, almost all PNC occurs immediately after delivery, and in 2017, fewer than 5% of women had any additional PNC visits [8,9]. The postpartum period, which is at least the first 28 days of life, is a crucial period during which effective follow-up care can significantly increase the chance of survival of newborns [10]. The World Health Organization (WHO) recommends at least four appropriately timed PNC sessions for all mothers and newborns, regardless of their birthplace [11].

In resource-limited settings, community health workers (CHWs) constitute a paid or volunteer public health workforce with an essential role in promoting health services and serve as a contact point between communities and health professionals [12]. In Lao PDR, CHWs are categorized as village health workers (VHWs) and village health volunteers (VHVs) based on their level and length of training, as well as their responsibilities in health promotion activities [13,14]. The 2019 Lao Primary Health Care Policy (PHCP) defines a VHW as an individual “who leads and implements disease prevention and health promotion, provides medical care and refers patients; collects the people’s health information as well as reports to a health center monthly” [15]. VHVs support VHWs, participate in health efforts with health facility staff, collect basic epidemiologic information, and promote proper maternal health practices.

Despite the important role CHWs play in promoting reproductive, maternal, and child health services, their acceptance is often challenged by local gender norms, especially when male or female CHWs approach members of the opposite gender for health promotion [16-18]. For instance, in Tanzania, male CHWs were more effective in discussing sexual and reproductive issues with men and engaging with senior family members, while mothers were more likely to disclose their pregnancies early with female CHWs [19]. Several studies have suggested that pairing male and female CHWs can be an effective strategy to navigate gender norm-related nonacceptance of MCH services provided by CHWs [19-22].

The new Lao PHCP also prioritizes strategies that involve male-female VHVs/VHWs working in pairs or groups to increase the quality of health promotion activities in communities and data reporting [15]. However, the only cross-sectional study that reported the association between pairing female-male VHVs/VHWs and improved mental health among postpartum women in Lao PDR could not determine the potential causal effect or its process [20]. In this context, we evaluate the effectiveness and process of pairing female-male VHVs/VHWs to promote the uptake of PNC in rural Lao PDR, which may guide the PHCP.

## Materials and methods

Design

A quasi-experimental cluster study with intervention and control arms is being conducted between July 2024 and July 2026 [23,24]. The evaluation will be pre-post intervention assessments following the type 1 implementation-effectiveness hybrid design [23]. The quantitative component of the study aims to estimate changes in effectiveness indicators, and the qualitative component will explore the context of implementation and community acceptance.

Settings

This study is being conducted in the Sepone and Vilabuly districts in southern Lao PDR as part of the evaluation of the Japanese International Cooperation Agency (JICA) Grassroot Project entitled "Project for Improvement of MCH by Enhancing Women's Empowerment in Poor and Remote Areas in Sepone District." The two districts are located in Savannakhet Province, approximately 600 kilometers from Vientiane, the capital city of Lao PDR, and close to the Vietnam border [25]. The map of study sites in Lao PDR is shown in Appendix A.

Sepone and Vilabuly share similarities, as both are mountainous areas with ethnic groups, including Lao-Tai, Phutai, Tri, and Makong, and poverty rates of 44.0% and 40.8%, respectively, as of 2018 [25-27]. According to the Savannakhet Health Provincial Office, Sepone and Vilabuly each have a district hospital, with 14 health centers in Sepone and 12 in Vilabuly [28].

Out of the 88 villages in Sepone, 19 intervention sites were selected in the catchment areas of five health facilities. These sites are called "model villages," as they previously implemented the 2017-2019 phase of the JICA Grassroot Project to promote ANC and facility-based delivery [29]. Since the project aims to extend the pairing of female and male VHVs/VHWs to all villages of Sepone District by 2024, we selected 18 control sites in the catchment areas of five health facilities of Vilabuly out of its 73 villages. The list of intervention and control villages in Sepone District and Vilabuly District is presented in Appendix B.

Participants

The target population of the quantitative component of the study is women aged 15-49 years who reside at the study sites. The participants will be women who gave birth within 12 months at the time of both the baseline and endline surveys. Women whose births resulted in stillbirths, those who did not consent to participate in the surveys, or those who faced a language barrier with surveyors - due to the presence of ethnic minorities who speak different local languages - will not be enrolled. In contrast, the qualitative component targets additional groups, such as village health volunteers and workers, male partners, family members, and health center staff.

Sample size and sampling method

We estimated the sample size using the logistic regression formula n > 10 m, where the minimum "n" of respondents with or without the study outcome is 10 times the number of covariates "m" to be included in the regression [30]. We estimated at least 80 facility-based follow-up PNC users with eight potential covariates. In 2022, VHVs/VHWs reported that there were 302 children of ≤1 year of age in the 37 targeted villages, including 137 from the 19 villages in Sepone and 165 from the 18 villages in Vilabuly. Due to the relatively low yearly delivery at the target sites, we will conduct exhaustive sampling at the baseline to include all eligible subjects, ensuring representative results [31].

For the end-line survey, we estimated the required sample size for difference-in-differences analyses to assess changes in the primary outcome before and after the intervention. We anticipate a 15.0% increase in facility-based follow-up PNC in the intervention villages and a 5.0% increase in the control villages over two years of implementation. Using a two-tailed z test for the difference between proportions, with 80% statistical power at the 5% significance level, unequal cluster size assessment, a design effect of 2, and a non-response rate of 10%, we estimated a sample size of 302 for the end-line survey [32,33].

Finally, at least 12 participants will be selected purposively for interviews in the qualitative component [34]. The enrollment of further participants will depend on when data saturation is reached.

Intervention, monitoring, and assessments

Between July and September 2024, a baseline survey will be conducted to assess pre-intervention levels of service utilization, women's socioeconomic and geographic characteristics, satisfaction with VHVs/VHWs, and other covariates related to the uptake of facility-based follow-up PNC visits. By November 2024, female-male VHV/VHW pairs were formed and trained on the intervention content at targeted sites in Sepone. Where necessary, new VHVs/VHWs will be selected following the national guidelines. The requirements include being a citizen of the Lao PDR, age ≥18 years, and being a resident of the village where they will serve [35]. In Vilabuly, we will ensure that each selected village has an active VHV/VHW, but no training will be conducted, as we aim to compare the intervention to the standard implementation of VHV/VHW activities.

Over the following 18 months, pregnant and postpartum women at all study sites will receive regular visits from VHVs/VHWs, either individually or in groups, for health counseling and educational activities focused on maternal health services, particularly postpartum care. In intervention sites, visits will occur at least once during the first and second trimesters of pregnancy, twice in the third trimester, and once during the first six weeks postpartum. VHVs and VHWs will highlight the benefits of facility-based follow-up PNC visits, extended postpartum stays at facilities, and the importance of husbands and family support during maternal care. While the main role of female VHVs/VHWs is to engage with mothers, male VHVs/VHWs in Sepone will be expected to have at least two interactions with male partners or family members during the third trimester of pregnancy and the first six postpartum weeks. The training content and frequency of visits by VHV/VHW will be validated using local recommendations to ensure policy alignment and greater community acceptance. In addition to skills related to MCH promotion, VHVs/VHWs in the intervention will receive training in task sharing and communication.

Around July 2026, an end-line survey will be conducted at all study sites to assess changes in outcome levels, and qualitative interviews will explore communities' perceptions and acceptance of paired VHVs/VHWs. 

To monitor implementation fidelity, VHVs/VHWs will complete standard reporting forms each month, documenting home visits and activities conducted. A midterm review using both monitoring data and qualitative insights will assess progress and inform any necessary course corrections.

Data collection

Both baseline and end-line assessments will be carried out using household surveys. Data will be collected by trained research assistants (medical students) using pretested semi-structured questionnaires prepared in English and translated into Lao using the Epi Info software. The questionnaires will be administered on tablets in Lao or other local languages as needed. The questions will focus on participants' socioeconomic and demographic characteristics, prior MCH service usage, and indicators of accessibility to healthcare facilities. Self-reported service utilization will be cross-validated using the maternal and child health handbooks (also known as the “pink book”).

Variables

WHO recommends that postpartum women have at least four postnatal care sessions regardless of delivery location, including within 24 hours after birth, on day 3, between seven days and 14, and after six weeks [11]. The primary outcome of the quantitative component is the use of at least one facility-based follow-up PNC visit within six weeks postpartum (yes/no). The secondary outcome is the duration (in hours) of facility-based postpartum stay by mothers after delivery. The two main predictor variables identified include residing in intervention versus control villages, and the frequency of VHVs/VHWs visits to mothers [36]. Additional variables will include respondents' sociodemographic characteristics, husbands' characteristics, household characteristics, gender norms, and trust in VHVs/VHWs.

Qualitative data will be gathered through key informant interviews and focus group discussions (FGDs). Interview and FGD guides will be developed in Lao, and interviewers (medical students) will receive training in qualitative data collection techniques. With participants’ consent, all interviews and discussions will be audio recorded, anonymized, and securely stored on a drive accessible only to the research team. The qualitative study will be conducted during the implementation phase to examine how the intervention is delivered and perceived, and to gain insights into the processes influencing its effectiveness. Interview and discussion guides will focus on the dynamics of interactions between VHVs/VHWs and mothers, between VHVs and mothers’ family members, and among VHVs who work together.

Data analysis

We will conduct difference-in-differences analyses using estimated levels of key indicators before and after the intervention, and test the significance of changes in outcomes. Pearson chi-square tests or t-tests will be used, as appropriate, to compare gaps in service use based on women's characteristics and other covariates. For multivariate analyses, mixed-effects logistic regression will be used to evaluate the associations between the primary outcome and predictor variables, while including interaction terms between time and group to assess the intervention effect. Statistics will be reported along with their 95% confidence intervals. P values of <0.05 will be considered to indicate statistical significance. All analyses will be performed using Stata Statistical Software (release 17, 2021, StataCorp, College Station, TX).

For the qualitative component, interview and FGD audio recordings will be transcribed, translated into English, and analyzed using both inductive and deductive content analysis approaches. Relevant codes will be extracted and organized into themes and sub-themes to provide insights into the intervention’s implementation context, feasibility, and acceptance within the community.

Ethical considerations

Ethical approval was obtained from the Ethics Committee of the University of the Ryukyus for Medical and Health Research Involving Human Subjects (approval no: 24-2329-00-00-00) and the Lao Tropical Medicine and Public Health Institute (approval no: 31/NECHR). The participants will be provided with comprehensive information sheets and consent forms outlining the purpose of the study. Participants aged 15-17 years will be requested to sign an assent form in addition to permission from their legal guardians. All the data collected will be handled anonymously, and confidentiality will be assured. Qualitative data, such as audio recordings, will be encrypted and stored securely on drives accessible only to the research team.

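### Eligibility sets no minimum time since birth although the primary outcome needs six weeks, so some later attenders are counted as non-users; the visit period and the end-line date also need reconciling

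*Protocol article*

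**What the plan says.** All of the following is in Materials and methods of the protocol article.

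- **Eligibility (Participants).** "The participants will be women who gave birth within 12 months at the time of both the baseline and endline surveys". The women who will not be enrolled are: "Women whose births resulted in stillbirths, those who did not consent to participate in the surveys, or those who faced a language barrier with surveyors". None of these exclusions concerns time since birth.
- **Primary outcome (Variables).** It is "the use of at least one facility-based follow-up PNC visit within six weeks postpartum (yes/no"). The secondary outcome is the length of the facility stay after delivery.
- **Visit period (Intervention, monitoring, and assessments).** "By November 2024, female-male VHV/VHW pairs were formed and trained on the intervention content at targeted sites in Sepone". The next paragraph continues: "Over the following 18 months, pregnant and postpartum women at all study sites will receive regular visits from VHVs/VHWs".
- **End-line (same subsection).** "Around July 2026, an end-line survey will be conducted at all study sites".
- **Length of implementation (Sample size and sampling method).** The expected increases are said to arise "over two years of implementation".

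**The concern.** A woman interviewed two weeks after delivery who goes back to the facility in week five is a user by the outcome definition, but the survey records her as a non-user. A woman who has already been back is recorded correctly. The misclassification therefore runs one way: it lowers measured uptake in every arm and round, and with it the difference-in-differences. Baseline sampling is already exhaustive because deliveries are few, so there is little spare sample to absorb a smaller observed effect.

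A second, separate matter is timing. Counted from November 2024, 18 months ends in about May 2026, before an end-line survey in July 2026. The sample-size text speaks of two years instead. As the text stands, one cannot tell whether the last births in the end-line window received the postpartum part of the visits.

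**Working it through.** **Inputs.** Children up to one year old: 137 in Sepone + 165 in Vilabuly = 302, which matches the article's total (Sample size and sampling method). I use 302 here only as a count of yearly births. Expected levels come from Results: 5% at baseline in both districts, 5 + 15 = 20% in intervention and 5 + 5 = 10% in control at end-line, a 10-point difference-in-differences. Outcome window: six weeks = 42 days. Assumption: births are spread evenly over the year.

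**Share with an open window.** f = 42/365 = 0.115. That is 0.115 × 302 ≈ 35 women (about 16 of 137 and 19 of 165).

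**Effect on the levels.** Let m be the share of eventual users in this group who have not yet attended at interview. Then observed level = true level × k, with k = 1 − f × m. If m is the same in all four arm-by-round cells, the baseline terms cancel and the observed difference-in-differences is k × 10 points. The documents do not give the timing of first visits, so I show a range. If every first visit fell on day d, f × m is simply d/365. The first two rows use day 3 and day 14, taken from the recommended contacts listed under Variables.

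| Assumed timing of first visit | k | Intervention | Control | Difference-in-differences |
|---|---|---|---|---|
| All on day 3 | 1 − 3/365 = 0.992 | 19.8% | 9.9% | 9.9 |
| All on day 14 | 1 − 14/365 = 0.962 | 19.2% | 9.6% | 9.6 |
| m = 0.25 | 0.971 | 19.4% | 9.7% | 9.7 |
| Even over six weeks (m = 0.5) | 0.942 | 18.85% | 9.42% | 9.42 |
| All at week six (m = 1) | 0.885 | 17.7% | 8.85% | 8.85 |

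As a yardstick, the usual two-proportion formula (two-sided 5%, 80% power, no design effect or non-response) needs 199 per arm for 20% versus 10%. For the last three rows it needs 206, 214 and 230.

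**On the odds-ratio scale.** With equal baselines the time-by-group odds ratio is (0.20/0.80)/(0.10/0.90) = 2.25. With even timing it is (0.1885/0.8115)/(0.0942/0.9058) = 2.23, and at worst about 2.2.

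**Effect of a 42-day minimum.** Within the same 12 months, 302 × (1 − 0.115) ≈ 267 women remain (about 121 and 146). Moving the window to 42 days through 12 months plus 42 days keeps about 302.

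**Dates.** Suppose the visits did end between 1 and 31 May 2026, and the survey fell between 1 and 31 July 2026. The gap is then 31 to 91 days.

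- Births after the visits end: 31/365 to 91/365 = 8.5% to 25% of a year's births, or about 12 to 34 of 137 in Sepone.
- Births whose six weeks are not wholly inside the visit period: (31 + 42)/365 to (91 + 42)/365 = 20% to 36%. This overlaps with the open-window group. Once women under 42 days are removed, 31 to 91 days of births remain, so 8.5% to 25% of a full year.
- A woman delivering on the survey day, with a 280-day pregnancy assumed, would still have had 280 − 91 = 189 to 280 − 31 = 249 days of pregnancy inside the visit period.

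**The case against.** The strongest reply is that the bias is small. Women who have already attended are classified correctly. The worst case requires every first visit to fall at week six, while two of the recommended follow-up contacts lie in the first 14 days, where the loss is under half a point. The loss is proportional and similar in all four cells, so the interaction odds ratio hardly moves. All of this stands, and it limits the point to modest attenuation.

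Enrolling from the day of birth also suits the secondary outcome, which is complete at discharge, and a 42-day filter could sit in an analysis plan. The first part stands, so enrolment need not be narrowed. The second stands only in part: the eligibility rule and the endpoint, both stated in the article, do not fit each other, and the outer limit of the end-line window is a field decision. Births between 12 months and 12 months plus 42 days that are never interviewed cannot be recovered in analysis.

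A reader might infer more than the documents support, in three ways:

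- **That the contrast is biased in an unknown direction.** This needs a mix of recent births that differs by district or round. Nothing in the article suggests that it does.
- **That late end-line mothers are miscounted as exposed.** The article does not say that visits stop in May 2026. It gives no date for the first visit; a start around January 2025 would take 18 months to about July 2026. Four of the five scheduled visits in the intervention villages are antenatal, so such women would be partly exposed. Grouping by village is an intention-to-treat comparison, and visit frequency is a separate predictor.
- **That only the intervention arm would be diluted.** The sentence on the 18 months covers all study sites.

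**Conclusion.** The mismatch between eligibility and primary outcome is real. On evenly spread births, the outcome is not yet fully observed for about one eligible woman in nine. The consequence is a modest and mostly non-differential attenuation: a true 10-point difference-in-differences reads as roughly 8.85 to 9.9 points, depending on when first visits occur. These figures rest on the article's own expected rates and on the same timing of visits in both arms and rounds. The fault is worth correcting because the correction is cheap and because part of it must be settled before end-line fieldwork.

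The timing point is a matter for reconciliation. The 18 months, the two years and the July 2026 survey do not line up as written. Whether any end-line births are only partly exposed depends on an answer that the article does not give.

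**What to change.** 1. For the primary outcome, in both rounds, analyse only women at least 42 days postpartum at interview, using birth and interview dates. Keep all births in the analysis of length of stay.
2. At end-line, let the survey enrol births up to 12 months plus 42 days, so that a full year of births with a complete window is available. Because the outer limits then differ between rounds, add a sensitivity analysis on the common window of 42 days to 12 months.
3. Reconcile the 18-month visit period, the two-year implementation period and the July 2026 end-line, and state whether visits continue to the survey. If they do not, keep the village-based comparison as the main analysis and add a sensitivity analysis limited to births whose six weeks fell within the visit period.

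**Cost.** One sentence on the analysis population, one on the end-line window and an analysis filter. About 11% of baseline records (about 35 of 302) are lost for the primary outcome; the end-line loses none if the outer limit is moved. The sensitivity analysis in item 3, if needed, would drop a further 8.5% to 25% of a full year of end-line births on the dates assumed above, which is why it should not be the main analysis.

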## Results

At the end of the study, several outcomes are anticipated in line with the study objectives. First, assuming baseline utilization is about 5% in both districts, we expect a 15% increase in Sepone (intervention) and a 5% increase in Vilabuly (control), resulting in a 10% difference in the proportion of women receiving at least one facility-based follow-up PNC visit. Second, guided by the theory of change, we hypothesize this improvement to result from enhanced counseling and more frequent interactions between mothers, male partners, and VHVs/VHWs through a gender-norms-sensitive approach. Specifically, regular household visits by paired VHVs/VHWs are expected to strengthen trust and satisfaction among mothers and promote male partner involvement, thereby contributing to increased PNC service uptake. Lastly, we also anticipate a longer average duration of postpartum facility stays among mothers in intervention areas.

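### The baseline sample-size rule asks for 80 follow-up PNC users, but the plan's own inputs give about 15 at baseline and about 59 with both surveys pooled

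*Protocol article*

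**What the plan says.** In Materials and methods, under Sample size and sampling method, the protocol article gives its baseline rule: "We estimated the sample size using the logistic regression formula n > 10 m". It takes n as the minimum number of respondents with or without the outcome and m as the number of covariates in the regression. The result follows: "We estimated at least 80 facility-based follow-up PNC users with eight potential covariates".

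The next sentences give the available population: "VHVs/VHWs reported that there were 302 children of ≤1 year of age in the 37 targeted villages". Sepone accounts for 137 of them and Vilabuly for 165. Because deliveries are few, "we will conduct exhaustive sampling at the baseline to include all eligible subjects".

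The event rate appears elsewhere. The Results section plans on the basis of "assuming baseline utilization is about 5% in both districts", rising by 15% in Sepone and 5% in Vilabuly, for a 10% difference. The Introduction reports that in 2017 "fewer than 5% of women had any additional PNC visits".

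The end-line survey has a separate calculation that also arrives at 302, with 10% non-response. The Data analysis section specifies a mixed-effects logistic regression with time-by-group interaction terms for the primary outcome.

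**The concern.** The requirement, the population and the event rate are all stated, but they are never multiplied together. Exhaustive sampling makes the roughly 302 mothers a ceiling, so a larger baseline sample cannot make up a shortfall. The rule counts the smaller outcome group, so the roughly 287 non-users do not help.

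Two things are at stake. First, events per variable is the only numerical justification given for the baseline sample, and a reader would take it to be satisfied. Second, a model with eight covariates fitted to very few events is exposed to small-sample bias and separation, most plainly if it is fitted to the baseline survey alone.

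**Working it through.** **Inputs**
- Covariates m = 8, ten events each (Sample size and sampling method).
- Population 302 = 137 (Sepone) + 165 (Vilabuly) (same section).
- Baseline uptake 5% in both districts (Results).
- End-line uptake 5% + 15 points = 20% in Sepone and 5% + 5 points = 10% in Vilabuly. Reading the increases as absolute is an assumption, supported by the stated 10% difference.
- End-line sample 302 (same section). Its 137/165 split is an assumption.
- Non-response 10%, stated for the end-line only. Applying it to baseline is an assumption.

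**Step 1: the plan's own figure.** 10 × 8 = 80. It reproduces.

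**Step 2: expected users at baseline.** Events = N × p = 302 × 0.05 = 15.1.
- Per covariate: 15.1 / 8 = 1.9.
- Shortfall: 80 / 15.1 = 5.3-fold.
- By district: 137 × 0.05 = 6.9 and 165 × 0.05 = 8.3.
- With 10% non-response: 15.1 × 0.9 = 13.6.

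**Step 3: what 80 would take.** Uptake of 80 / 302 = 26.5%, or 80 / 0.05 = 1,600 women at 5%. Even if all 302 women were at the 20% hoped for in Sepone at end-line, there would be 302 × 0.20 = 60 users.

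**Step 4: sensitivity to the baseline rate (302 women)**

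| Uptake | Users | Per covariate |
|---|---|---|
| 3% | 9.1 | 1.1 |
| 5% | 15.1 | 1.9 |
| 6% | 18.1 | 2.3 |
| 10% | 30.2 | 3.8 |

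**Step 5: both surveys pooled, as the time-by-group model implies.**
- End-line users: 137 × 0.20 + 165 × 0.10 = 27.4 + 16.5 = 43.9.
- Pooled: 15.1 + 43.9 = 59.0.
- Per covariate: 59.0 / 8 = 7.4. Shortfall: 80 / 59.0 = 1.4-fold.
- With 10% non-response in both waves: 59.0 × 0.9 = 53.1, or 6.6 per covariate and 1.5-fold short.
- If the increases are read as relative: 15.1 + 137 × 0.05 × 1.15 + 165 × 0.05 × 1.05 = 31.6 users.

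**Step 6: conditional on the term count.** If the group, time and interaction terms come on top of the eight, there are 11 terms: 59.0 / 11 = 5.4, or 53.1 / 11 = 4.8. The article does not list the eight, so this is only a possibility.

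**The case against.** The strongest reply is that the five-fold gap does not describe the main analysis. The interaction model needs both surveys, where the gap is 1.4-fold, and nothing in the article commits to an eight-covariate baseline-only regression as a main result. This stands: the two shortfalls have to be kept apart. It does not rescue the sentence, because 59 is still below 80 and the article attaches the 80 to the baseline.

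Three stronger readings are tempting, and the documents do not support them.

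- *A reader might infer that the eight covariates leave out the group, time and interaction terms.* The article never lists the eight. It names intervention residence as a main predictor without saying whether it is one of them.
- *A reader might infer that the confidence intervals of the adjusted result cannot be trusted.* Missing a ten-events rule of thumb does not show that. A simple simulation of the pooled scenario (302 women per wave, 4,000 runs, ordinary logistic regression, true interaction log odds ratio 0.811) gave 95% interval coverage of about 95–96% with none, two or eight covariates. Non-convergence or separation was 0.2% or less, and the standard deviation of the estimate was about 0.7 throughout. It had no village clustering, and its covariates were balanced, binary and unrelated to group and outcome, so rare or correlated covariates could do worse. It also shows that most of the imprecision comes from the few users, not from the number of covariates.
- *A reader might infer that the model must be cut to the three design terms plus two covariates, because 53–59 users support five terms under the rule.* This treats a rule of thumb as a hard limit. It also gives up adjustment in a non-randomised two-district comparison for which the limitations section names confounding.

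The difference-in-differences comparison without covariates does not depend on the covariate count, and the end-line survey has its own calculation. Neither is affected by this point.

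**Conclusion.** The stated criterion is not met on any reading examined: about 15 users at baseline (1.9 per covariate, 5.3-fold short) and about 59 pooled (7.4 per covariate, 1.4-fold short).

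The baseline result needs only the article's 302 and 5%. It is if anything generous, because 302 counts children reported in 2022, and women who do not consent or who face a language barrier are not enrolled. The pooled result further assumes 302 women per wave split 137/165 and absolute increases. It falls to about 53 with 10% non-response in both waves. Events per term are lower again if the design terms are not among the eight.

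This is an error in the stated justification, with a modest consequence for how the adjusted model should be estimated. It does not show that the main result is invalid. It is also not a matter of detail left to a fuller document, because the article itself states a requirement, a population and a rate that cannot all hold.

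**What to change.** - Correct the sample-size sentence. Keep 80 as what the rule would require, give the expected users (about 15 at baseline, about 53–59 with both surveys pooled) with the assumptions behind them, and say that ten events per variable is not reached.
- Do not fit an eight-covariate maximum-likelihood model to the baseline survey alone.
- In the pooled adjusted model, keep confounder control through a propensity-type summary score or penalised (Firth-type) likelihood, without a fixed cap of two covariates. State whether the eight covariates include the group, time and interaction terms.

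The cost is a less favourable stated figure and slightly more analysis work. No new data are needed, and the change can be made before the end-line analysis.
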